# Effectiveness and cost-effectiveness of primary arthrodesis versus open reduction and internal fixation in patients with Lisfranc fracture instability (The BFF Study) study protocol for a multicenter randomized controlled trial

**DOI:** 10.1186/s12893-021-01320-1

**Published:** 2021-08-12

**Keywords:** Traumatic Lisfranc fracture dislocation, ORIF, PA, Quality of life, Cost effectiveness

## Abstract

**Background:**

The Lisfranc injury is a complex injury of the midfoot. It can result in persistent pain and functional impairment if treated inappropriately. In Lisfranc fracture dislocation, treatment options are primary arthrodesis of the midfoot joints or open reduction and internal fixation. The purpose of the proposed study is to define the optimal treatment for the Lisfranc fracture dislocation, either primary arthrodesis or open reduction and internal fixation, in regard to quality of life, complications, functional outcomes, and cost effectiveness.

**Methods:**

Study design: A prospective multicenter RCT. Study population: All patients of 18 years and older with an acute (< 6 weeks) traumatic fracture dislocation in the Lisfranc midfoot joints, displaced on static radiographic evaluation or unstable with dynamic evaluation, weight bearing radiographs or fluoroscopic stress testing under anesthesia, and eligible for either one of the surgical procedures. In total, this study will include n = 112 patients with Lisfranc fracture dislocation. Interventions: Patients with Lisfranc fracture dislocation will be randomly allocated to treatment in “The Better to Fix or Fuse Study” (The BFF Study) with either PA or ORIF. Main study parameters/endpoints: Primary outcome parameter: the quality of life. Secondary outcomes: complications, functional outcomes, secondary surgical interventions and cost effectiveness. Nature and extent of the burden: PA is expected to have a better outcome, however both treatments are accepted for this injury with a similar low risk of complications. Follow up is standardized and therefore this study will not add extra burden to the patient.

**Discussion:**

This study protocol provides a comprehensive overview of the aims and methods of the attached clinical study. Limitations of this study are the absence of patient blinding since it is impossible in surgical intervention, and the outcome measure (AOFAS) that has limited validity not for these injuries. This study will be the first with enough power to define optimal treatment for Lisfranc fracture dislocations. This is necessary since current literature is unclear on this topic.

*Trial registration* Current controlled Trial: NCT04519242 with registration date: 08/13/2020. Retrospectively registered; Protocol date and version: Version 4 05/06/2020

**Supplementary Information:**

The online version contains supplementary material available at 10.1186/s12893-021-01320-1.

## Background

*‘The human foot is a masterpiece of engineering and a work of art’*—Leonardo da Vinci. The foot does indeed consist of an intricate structure of bones and joints, where stability and mobility are balanced during gait. Injuries to the bones or joints of the foot, for example in fracture dislocation of the midfoot joint complex, therefore, have a significant impact on both the stability and mobility of the foot. The midfoot or Lisfranc joints are of great importance for the stability of the foot [1–3]. Injuries at the Lisfranc complex are not common, approximately 0.2% of all fractures with an incidence of 1/55,000 [1, 2]. The impact of these injuries on the function of the foot and the quality of life is, however, considerable. In addition, there are significant healthcare- and societal costs. Finally, these injuries are also indicative of the impact of other injuries of the foot, such as Chopart or intertarsal joint injuries.

“The Better to Fix or Fuse Study” (The BFF Study) is the first prospective large randomized controlled trial (RCT), worldwide comparing the two generally accepted treatment strategies in displaced or unstable Lisfranc fractures: Open Reduction and Internal Fixation (ORIF) and Primary Arthrodesis (PA). Until now there have only been three previous reported RCTs comparing ORIF vs. PA for Lisfranc injuries, and one non-RCT, and eight retrospective case series [4–15].

Overall, these studies concluded that PA seems to result in less secondary surgery, less implant removal, and a faster return to activity. Besides, there is some evidence of a better functional outcome after arthrodesis as reported in the Patient Reported Outcome Measures (PROMs) reported in several of the above-mentioned studies. these results are, however, still not significant [4–15]. Nevertheless, the current overall evidence slightly favors arthrodesis as a primary treatment of dislocated Lisfranc injuries. However, all these results do not reach significant improvement and the risk of bias of these previous studies is either moderate or high.

The BFF Study is also the first study to not only look at the Lisfranc injury when unstable on static radiographic evaluation, but also at the injury with displacement solely at dynamic evaluation. Weight bearing radiographs a/o fluoroscopic stress testing under anesthesia, are included. At the time of publication of this study protocol there is no clear evidence what treatment is best for the non-displaced unstable Lisfranc injury as proven by
displacement at dynamic stress testing (Additional file 1).

## Diagnosis and treatment

An inadequately treated Lisfranc injury with persistent instability can result in multiple late complications, most commonly painful instability of the joint malformation or post-traumatic arthritis [16, 17]. All these complications can lead to gait dysfunction and foot pain [16, 17]. Therefore, adequate surgical treatment is needed to restore stability. Due to the diversity of injuries, there is no gold standard for treating all Lisfranc injuries in a similar manner [10]. It is therefore important to distinguish between ligamentous Lisfranc injuries and Lisfranc fracture dislocation.

PA is generally accepted as the treatment of choice in pure ligamentous injuries. In case of an unstable Lisfranc injury, with displacement either on static or dynamic radiographic evaluation, the best treatment is aimed at a stable construction with anatomic alignment [10]. This can be achieved by using either ORIF or by PA. ORIF is associated with problems such as the occurrence of secondary arthritis in 40–90% and the need for secondary interventions to perform arthrodesis or to remove the osteosynthesis materials in order to relieve pain [18, 19]. To prevent this need for secondary interventions and the development of post-traumatic arthritis, primary arthrodesis is suggested [6, 7, 12, 20]. On the other hand, retaining the joints of the midfoot may possibly improve the functional mobility and thereby the quality of life after removal of the osteosynthesis materials. As these potential complications can have a major impact on patients’ everyday lives, research is needed to define the best available surgical treatment for these patients with unstable Lisfranc fracture injury.

## Economic aspects

The need to deliver healthcare efficiently has increased substantially during the last years [21]. Two studies reviewed the costs of ORIF and PA, one of them found PA was significantly more expensive and, in contrast, one found PA to be more cost-effective [21, 22]. These studies measuring the cost-effectiveness only measured the patient costs such as professional care and diagnostic tests. We suggest measuring the social and family costs caused by reduced productivity and hospital visiting as well, since Lisfranc injuries may often cause long-term complaints that may influence these costs [22, 23].

## Evaluation of treatment

A number of studies have already been published comparing ORIF with PA in Lisfranc injuries. Most of these studies have used Patient Reported Outcome Measures (PROMs) and X-ray evaluations to evaluate both treatments. The most common PROM used in Lisfranc studies is the American Orthopaedic Foot and Ankle Score (AOFAS) [10, 21, 24–26]. Other commonly used PROMs include the Short-form 36 or Short-form 12 (SF-36 or SF-12 score) and the Visual Analogue Scale (VAS). As the efficiency of health care interventions become more and more important recent years, the patient health-care costs, the family costs and societal costs have to be investigated too for both treatment options. These costs have not been investigated in previous randomized studies. Our study is, to our knowledge, the first prospective RCT that will investigate these costs for both treatment options.

## Need for this study

Because of the limitations of the methodological quality of the previous reported clinical trials it is still impossible to favour one intervention; PA or ORIF, over the other for the treatment of unstable and or dislocated Lisfranc fractures. Therefore, for drawing a definitive conclusion for the best treatment there is an urgent need for a large prospective high-quality RCT. Such a trial should also assess cost-effectiveness, as cost considerations might be decisive in decision making especially when both treatments are equal based on PROMs.

## Methods

### Aim of the study

The primary objective of this study is to compare the effects ORIF vs. PA have on the quality of life of patients with unstable or displaced Lisfranc fractures over a period of 24 months.

The secondary objectives are to compare the differences in the amount and type of secondary procedures, including removal of osteosynthesis materials, difference in objective and subjective functional outcomes, difference in alignment of the foot on weight-bearing X-rays, difference in occurrence of complications and differences in costs and cost-effectiveness.

### Study design

The BFF Study is a nationally prospective multicenter, randomized controlled trial (RCT) performed in the Netherlands. In total, 13 medical institutions in the Netherlands will enroll patients during a 24 months period, and the enrolment is stared at June 2020. The participating institutions of “The BFF Study” are defined in the Additional file 2.

### Study setting

The BFF Study is a multicenter prospective RCT and will be conducted in The Netherlands in thirteen participating medical institutions. Please see the Additional file 2 for more information about the location of the participating medical institutions. The SPIRIT (Standard Protocol Items: Recommended for Interventional Trials) 2013 statement will be followed. Approval of the local medical ethics committee was obtained with Registration number: NL 73038.096.20. Furthermore, “The BFF Study”-The Better to Fix or Fuse Study, is retrospectively registered in the ClinicalTrials.gov database with Registration number: NCT04519242 on 08/13/2020 and will be conducted in line with the declaration of Helsinki.

### Trial recruitment and allocation

Every medicinal institution participating in “The BFF Study” will have a Local Investigator (LI). This LI is in most cases the treating physician of the patient. The Coordinating Investigator (CI) coordinates the trial and gives advice to all separated LI’s of each medical institution. Together the LI’s of each medical institution, which are all trauma surgeons, and the CI will form “The BFF Study” group. The LI’s will actively screen patients for eligibility at the emergency department or at the outpatient clinic of their institution. If there are any questions about the eligibility criteria the CI will be contacted by the LI. All the LI’s, and side investigators in each medical institution are mentioned in Additional file 2. The CI is also described in Additional file 2.

### Characteristics of participants

Patients can be included if they meet all the following inclusion criteria:Age ≥ 18 years.Acute Lisfranc fracture injury (< 6 weeks after trauma).Displaced or unstable injury with weight-bearing radiographs or fluoroscopic stress testing under anesthesia*.Independent for activities of daily living (yes/no question).

Partients who meet one or more of the following criteria will not be considered for inclusion:Age < 18 years.Open Lisfranc injury.Pure ligamentous Lisfranc injury.Non-displaced and stable injury with weight-bearing radiographs or stress testing under anaesthesia.Contra-indications for general or locoregional anaesthetic techniques.Other fractures in the ipsilateral leg.Pre-existent abnormalities at the Lisfranc complex.Pre-existent immobility.Dependent in activities of daily living (due to dementia, Alzheimer’s, NYHA class IV angina and heart failure, oxygen-dependent COPD).Rheumatoid arthritis.Pathologic fractures (metastasis, secondary osteoporosis).Peripheral neuropathy and/or diabetes.Alcohol or drug abuse preventing adequate follow-up.

### Definition of displaced or unstable*

Instability, e.g., displacement or malalignment on radiographs interpreted as follows:AP view:Lateral displacement of 2nd metatarsal on intermediate cuneiform, medial margin of the second metatarsal and the middle cuneiform not aligned. TMT 1 disruption, lateral margin of the first metatarsal not aligned with the lateral margin of the medial cuneiform; Gap between 1st and 2nd metatarsal and/or ceuneiforme medialis and intermedius (> 2 mm);30-degree oblique view:Lateral displacement of 3rd metatarsal on lateral cuneiform, lateral margin of the third metatarsal and the lateral cuneiform not aligned; Medial margin of the fourth metatarsal and cuboid not aligned;Lateral view:Dorsal displacement of the metatarsal bases above the level of the cuneiforms.Any view:Bony avulsion fractures between base 2nd metatarsal and cuneiforme medialis (fleck sign), and/or between cuneiforme medialis and intermedius.

### Recruitment procedure

Patients eligible for inclusion will be recruited by the LI at the emergency department or at the outpatient clinic of each participating medical institution. The LI in each hospital will be contacted about every Lisfranc injury as part of normal clinical practice. Local protocol in the medical institutions will daily revise patient files and X-rays so to decrease the chance that patients with Lisfranc injuries will be missed. The LI will inform the patient about the two surgical treatment options for displaced or unstable Lisfranc fractures. If a patient is eligible for participation in the BFF Study, the LI will provide the potential patient with the Patient Information Folder (PIF) and the Informed Consent (IC) form (Additional file 1). The patient can take the PIF home to read the information carefully. The patient will then have the option to make contact by telephone or mail with the LI or CI to ask questions about the study participation. Patients will be granted a reasonable amount of decision time, at least 7 days, to make a decision if they want to participate (Fig. 1).

**Fig. 1 Fig1:**
[figure not shown]
Flow chart describing the recruitment and follow-up process

Patients will be asked for formal written IC prior to participation in accordance with Good Clinical Practice. Patients who decide to participate will give their written informed consent to the participating medical institution. After permission to participate the patients will be randomly assigned to one of the two treatment arms which is ORIF or PA. The patient will be informed by the LI or CI which type of surgery they will get so they can ask specific questions about this type of surgery.

### Data collection and processing

Baseline characteristics will be received through the electronic patient file (EPF) and clinical assessment by the LI and stored in the case report form (CRF) as set down by the online data management system Castor Electronic Data Capture, an application through which one can easily and safely collect data online.

The EPF is screened every follow-up to assess late complications, re-interventions, re-admissions, duration of medical institution stay and consultations at the medical institution. This screening and follow up assessment will also be done by the LI, or side investigator of the medical institution or by the CI if necessary. All of this data information will also be reported in the CRF by the LI, side investigator or CI. If the LI or side investigator have any questions regarding the data, the CI will be contacted.

### Follow-up procedure

Follow-up will consist of clinical follow-up at 2 weeks and clinical follow-up and e-mail questionnaires at baseline at 8 and 12 weeks, and 6, 12 and 24 months after surgery (Fig. 1). After care will be the same for all patients, namely plaster cast immobilization or Air Walker for 8 weeks in total. Plaster cast immobilization or Air Walker will be non-weight bearing for 4 weeks followed by weight bearing for another 4 weeks.

All questionnaires will be digital. Enrolled patients will receive a link by e-mail at the preset follow-up moments to fill in before the standard follow-up moment at the outpatient clinic occurs, except at 2 weeks post-surgery. These messages are regulated by Castor Electronic Data Capture.

Radiographs will be performed each follow up period and interpreted as “aligned or not aligned” using previously mentioned alignment criteria for that specific follow-up moment.

To promote participants retention and complete follow-up the patients are called by the CI if the participant does not fill in the questionnaire within 5 days after invitation.

### Participant withdrawal

The LI or CI can decide to withdraw a participant from the study for urgent medical reasons. Participants can leave the study at any time for any reason if they wish to do so, without any consequences. Withdrawal of participants will be recorded, including the reason (if known) in the data management system; Castor Electronic Data Capture. The withdraw will also be recorded in the EPF.

### Randomization and blinding

After given written informed consent, participants will be randomized in a 1:1 ratio to PA or ORIF, using randomization stratified by the center with random permuted block sizes of four patients. This randomization will be performed using a web-based computer (L-DOT) directed randomization. This randomization tool was developed by the centre of data and information management at the Faculty of Health, Medicine and Life Sciences of Maastricht University and MUMC+ (MEMIC). A unique study record number will be generated, and the allocation will be disclosed. Due to the comparison of outpatient-based and surgical treatment strategies in this study, blinding to the treatment allocation for participants and medical staff is not possible. A specialized independent statistician will analyze the data blinded for treatment allocation.

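### A single published block size of four within centre lets an unblinded recruiting surgeon who keeps count know about 35 of 112 allocations in advance

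*Protocol article*

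**What the plan says.** Under Randomization and blinding, the protocol article assigns the two operations in equal numbers, "using randomization stratified by the center with random permuted block sizes of four patients". The word random could be taken to describe the sizes, but only one size is given. The order within a block is random and its length is not.

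The same section says that "This randomization will be performed using a web-based computer (L-DOT) directed randomization" and that it follows written consent. It then says: "A unique study record number will be generated, and the allocation will be disclosed". On blinding it states that "blinding to the treatment allocation for participants and medical staff is not possible", and the reason it gives is a contrast between outpatient care and surgery. Only the analysing statistician is blinded.

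Under Trial recruitment and allocation, the local investigators are all trauma surgeons and screen for eligibility. Of the local investigator the article says: "This LI is in most cases the treating physician of the patient". Under Recruitment procedure, the same person is contacted about every Lisfranc injury at the hospital, explains both operations and recruits. Nothing in the article says that block sizes vary or are withheld from the sites.

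**The concern.** Central web-based randomisation hides the list. It does not hide what can be deduced from earlier allocations once the block length is known and those allocations are open. The block length is now in print.

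The judgement of instability, the explanation of the two operations and the offer of the trial all come before randomisation. A surgeon who prefers one operation for a given foot, and who knows what comes next, could offer the trial sooner, later or not at all. This would be hard to see from outside: the article expects about 190 patients screened for 112 enrolled, so 78 non-enrolments are already anticipated. The Abstract also says that primary arthrodesis is expected to do better, so a preference among recruiters is conceivable.

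At stake is the comparability of the arms. The primary outcome is the EQ-5D-5L, reported by patients who know their operation, and the target difference is 0.08 points.

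**Working it through.** **Inputs.** Block size 4, ratio 1:1 and strata by centre (Randomization and blinding); 13 centres (Study design); 112 patients, SD 0.15, difference 0.08, power 80% (Sample size and feasibility); significance level 0.05 (Descriptive statistics), taken as two-sided, which is an assumption.

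**The plan's own figure.** The article gives no figure for predictability. The sample size, which the calculation below uses, reproduces: 2 × (1.960 + 0.842)² × 0.15² / 0.08² = 55.2, rounded up to 56 per arm, or 112 in total.

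**One complete block.** Six balanced sequences are equally likely. An allocation is certain when one arm already has its two patients. The best guess is the arm that is behind in the block.

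| Position | Certain in advance | Best guess right |
|---|---|---|
| 1 | 0 | 1/2 |
| 2 | 0 | 2/3 |
| 3 | 1/3 (first two the same: 2 of 6 sequences) | 1/3 × 1 + 2/3 × 1/2 = 2/3 |
| 4 | 1 | 1 |
| Mean | (1/3 + 1)/4 = 33.3% | (1/2 + 2/3 + 2/3 + 1)/4 = 70.8% |

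**The trial, with even recruitment.** 112/13 = 8.6, so take 8 centres with 9 patients and 5 with 8 (72 + 40 = 112). Each centre completes two blocks. The ninth patient opens a third block and is not predictable.

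- Certain: 13 × 2 × 4/3 = 34.7 patients; 34.7/112 = 31.0%.
- Best guess right: 13 × 2 × 17/6 + 8 × 1/2 = 77.7; 77.7/112 = 69.3%.

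**Uneven recruitment (assumed).** Simulating random centre sizes, with unfinished last blocks, gives about 29% certain (range 27–30%).

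**Varying sizes.** This was simulated with sizes equally likely, 8–9 patients per centre, and a recruiter who knows the set of sizes but not the current one.

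| Scheme | Certain | Best guess right |
|---|---|---|
| Fixed 4 (exact, as above) | 31.0% | 69.3% |
| 4 and 6 | 5.7% | 66.3% |
| 4, 6 and 8 | 2.7% | 65.6% |
| 2, 4 and 6 | 3.1% | 67.8% |

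In patients, certain allocations fall from about 35 to about 6 (0.057 × 112 = 6.4) or 3 (0.027 × 112 = 3.0). Size 2 has no advantage: a known block of two is guessed correctly 75% of the time.

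**What recruitment may remain.** Enrolment began in June 2020 and was planned for 24 months; the article appeared in August 2021. Under even accrual (an assumption), 14/24 × 112 = 65 patients, or 5 per centre, were in by then. The average centre was already in its second block. With 8–9 patients per centre, unopened blocks would then hold only about 8 patients. Uneven accrual would leave more at the larger centres.

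**The case against.** The best case for the plan is that several features limit what a recruiter can do. Randomisation is central and follows consent. Instability has written radiographic criteria, files and X-rays are reviewed daily so that injuries are not missed, eligibility questions go to the coordinating investigator, and patients have at least seven days to decide. No passage says that the local investigator sees every earlier allocation at the site: side investigators take part, and the coordinating investigator may be the one who tells the patient. A full protocol may also say more about what sites were told during conduct. These points stand as limits on the opportunity, but they do not remove it. Allocations are disclosed, staff are unblinded, each centre expects only eight or nine patients, and the size has been published.

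A reader might infer that a full third of the trial, 37 of 112, is knowable. That figure assumes complete blocks everywhere, which 8.6 patients per centre does not allow. A reader might also infer that the rest of a block is known once two patients are in. That holds in only one block in three.

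Nor would varying the sizes bring guessing down to 50%. The running imbalance at a centre is informative whatever the block size, and the guessing rate hardly moves.

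**Conclusion.** The point holds as a design weakness of moderate size that is cheap to reduce. With one fixed block size of four per centre, about 35 of 112 allocations (31%) can be known before the offer is made, or about 29% if recruitment is uneven. This rests on a recruiter who keeps count of the site's allocations and uses the published size.

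The finding is a risk of selection bias. The documents give no evidence that anyone acted on it and no basis for sizing its effect on the EQ-5D-5L. It would also be too strong to say that the analysis can do nothing: the primary model adjusts for BMI, age and sex, which deals with imbalance in those three. It would not deal with selection on injury features or other unmeasured prognosis, so the protection is partial.

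The reason given for not blinding is a separate error of wording. It speaks of outpatient-based against surgical care, while Trial interventions describes two operations and the Abstract and Discussion point to the surgery itself. Allocation is open either way, so this does not change the block-size argument.

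**What to change.** For all blocks not yet opened, set the web system to draw block sizes at random within centre, for example 4 and 6, or 4, 6 and 8. Withhold the sizes from the sites, and do not publish the new scheme until recruitment ends. The sample size stays at 112.

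The cost is a configuration change and a short amendment, with a slightly larger possible arm imbalance in small centres. The benefit is confined to the recruitment that remains, and it lies in removing certain allocations rather than in making guessing much harder.

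In the same amendment, correct the sentence on blinding so that its reason fits a comparison of two operations.
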